### Study design and setting

2.2

The PRECODE study is a randomised, double-blinded placebo-controlled, four-armed parallel trial in older adults (60–79 years) with SCD+, with a duration of 26 weeks (Clinical trials identifier NCT06433037). Participants (*n* = 164) will be randomised by block-randomisation (based on sex, age, education and risk factor profile) in four different groups of equal size (*n* = 41). Either one of the following will be administered daily:

Placebo (Maltodextrin) – 7 g per day, divided over two dosages of 3.5 g.Chicory inulin – 12 g per day, divided over two dosages of 6 g.Resistant dextrin – 14 g per day, divided over two dosages of 7 g.Seaweed polysaccharide – 1 g per day, divided over two dosages of 0.5 g. (Seaweed will additionally contain 7 g (3.5 g per dose) of placebo as a volumetric and isocaloric filler.)

Participants will undergo assessments at baseline (*T*_1_), week 13 (*T*_mid_) and at study end (*T*_1_), after 26 weeks at the Division of Human Nutrition & Health (HNH) at Wageningen University (WUR) and the Gelderse Vallei Hospital (ZGV) in the Netherlands (Figure 3). Each participant will have four study visits in total: two at *T*_0_, and two at *T*_1_. In a subselection of participants (*n* = 80), there will be an additional mid-visit (*T*_mid_) in week 13, with five study visits in total. At *T*_0_ and *T*_1_ participants will first visit WUR for investigations and a week later visit ZGV for fMRI scanning. In the week between the visits, participants will collect two faecal samples, wear smartwatches and complete online questionnaires at home. The *T*_mid_ visit consists of a single visit to WUR only. To ensure compliance and to address any questions or concerns that arise during the intervention, five phone calls (10–15 min) will be made to participants during the course of the study.

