##### Cognitive and mood assessments

2.8.1.2

Cognitive and mood outcomes will be assessed *T*_0_, *T*_mid_ and *T*_1_ visits (Table 3). The neuropsychological test battery (NTB) consists of the Cognitive-Functional Composite (CFC) and the Montreal Cognitive Assessment scale (MoCA) - the latter assessed at *T*_0_ only. The CFC battery provides a short and clinically relevant measurement of the cognitive domains that are sensitive to decline in early AD (186). The brief CFC NTB consists of six cognitive tests focusing on episodic memory, working memory and executive functions (186). Components included within the CFC are three components of the Alzheimer’s Disease Assessment Scale-Cognitive subscale (ADAS-Cog) (word recall, orientation, and word recognition), as well as a digit span test, verbal fluency test, and digit symbol substitution test. These tests can detect subtle worse performance in SCD subjects (112). The MoCA scale is a test with high sensitivity and specificity for minor cognitive defects (if scored ≤26/30) (187).

The Geriatric Depression Scale-15-item version (GDS-15) is a concise tool specifically developed to screen for depression in older populations, with established cut-offs and has demonstrated high sensitivity and specificity in older adults (188). The Generalized Anxiety Disorder-7 (GAD-7), a seven-item questionnaire, validated for use in older adults, will be employed to evaluate the presence of anxiety symptoms in daily life (189, 190). Subjective cognitive decline, will be measured via the Cognitive Failure Questionnaire (CFQ), a 25-item scale quantifying the frequency of everyday cognitive lapses (191, 192).

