#### Statistical methods for primary and secondary outcomes

2.9.1

Data analyses will be performed using R-studio, GraphPad and SPSS. Numerical values will be reported as mean ± SD or confidence intervals. The level of significance is set at 0.05 (two-sided). The Benjamini-Hochberg correction will be used to correct and adjust all *p*-values for multiple comparisons, with the inclusion of a false discovery rate.

The *primary objective* of this study is to investigate the effect of 26 weeks of supplementation with three different dietary fibres (chicory inulin, resistant dextrin, and seaweed polysaccharide) compared to a placebo on working memory (fMRI). Analyses for the primary outcome will compare each fibre group individually to placebo using ANCOVA to adjust for baseline differences, and evaluate the effect of the intervention group at 26 weeks. Specifically, averaged beta weights will be extracted from the regions of interest to determine significant activation at low cognitive load (1-back versus 0-back) and high cognitive load (2-back versus 0-back). *d*-prime values will be calculated to assess working memory task performance. Linear mixed models will be used to evaluate effects on the *secondary and tertiary outcomes* of each dietary fibre individually compared to the placebo at the two different timepoints (baseline and week 26) to measure the interaction group x time. Participants will be set as the random factor, with group and time set as the non-random (fixed) factors. Post-hoc analyses will be performed in case of a significant group x time interaction to understand which fibre(s) specifically differ from the placebo group.

Additionally, *exploratory analyses* will evaluate whether gut- or brain-related biomarkers (e.g., kynurenic acid, serotonin, tryptophan indoles) are associated with cognitive (NTB, MoCA), mood (GDS-15, GAD-7), or physiological outcomes. To elucidate potential mechanisms of the dietary fibre intervention along the MGBA, mediating effects of SCFA levels, TRP metabolite levels and intestinal barrier markers (e.g., LBP, zonulin) between fibre intervention group and cognitive outcomes will be evaluated in case of significant main effects.

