The inclusion of a mid-study visit after 13 weeks, allows for determining the duration of intervention needed for microbiota and metabolite shifts. Furthermore, mid-study effects on cognition by NTB will allow for insights into timing of onsets of potential protective cognitive effects. Moreover, sex, ApoE genotype and age, influence AD disease stage progression (251). Here, further valuable information on whether these factors may influence the trajectory of potential interventions may be highlighted. Moreover, should there be any significant association evidenced between microbial compositional change and cognitive performance, it might be worthwhile to conduct a follow-up investigation, in which we research if and how long potential microbiota changes last after the trial has been finished, and to compare E4 vs. non-E4 carriers and relatedness of the number of LIBRA risk factors.

Despite its strengths, the study has potential limitations. The self-reported and progressive nature of SCD + may introduce heterogeneity, such as the potential inclusion of individuals with undiagnosed depression and anxiety that may mimic cognitive decline (114, 252). Clinical depression and anxiety are excluded at screening, and will be further assessed by GDS-15 and GAD-7 scores at baseline. Furthermore, some individuals may potentially convert to amnestic MCI over the course of the intervention, which will be evaluated by end-NTB results. Inclusion criteria, such as requirements for general and technological literacy, may additionally introduce bias towards individuals with higher education or better cognitive function. In addition, the inclusion criterion of at least 2 LIBRA risk factors next to presence of SCD may overall limit the generalizability of our findings to SCD individuals with fewer or different combinations of lifestyle risk factors, and should not be generalized to the entire preclinical AD spectrum. Next, long-term fibre supplementation in older adults with increased gastrointestinal sensitivity, may lead to study withdrawal, for which a 15% drop-out rate has been included. Strategies such as dose tapering, morning and evening dosing, and telephone check-ins are used to promote adherence. Furthermore, due to the scope of inclusion and exclusion criteria, including MRI compatibility, extensive recruitment efforts might be needed.

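### The mixed model for secondary and tertiary outcomes leaves baseline means free, which costs some precision at week 26, and its two named timepoints leave the week-13 subset without an analysis

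*Protocol article*

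**What the plan says.** Section 2.9.1 gives the primary outcome an analysis "using ANCOVA to adjust for baseline differences, and evaluate the effect of the intervention group at 26 weeks". Secondary and tertiary outcomes get a linear mixed model, each fibre "compared to the placebo at the two different timepoints (baseline and week 26) to measure the interaction group x time". Its terms are stated: "Participants will be set as the random factor, with group and time set as the non-random (fixed) factors". No baseline covariate or baseline constraint is named. The paragraph then adds: "Post-hoc analyses will be performed in case of a significant group x time interaction", in order to find which fibres differ from placebo.

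The week-13 wave is described elsewhere. Section 2.2: "In a subselection of participants (*n* = 80), there will be an additional mid-visit". Section 2.8.1.2: "Cognitive and mood outcomes will be assessed *T*_0_, *T*_mid_ and *T*_1_ visits". Table 3 also marks week 13 for BDNF, blood tryptophan metabolites, faecal microbiota, short- and branched-chain fatty acids, faecal pH and water content, the gastrointestinal questionnaires, and HbA1c, glucose and insulin. The Discussion (section 4) gives the purpose: "The inclusion of a mid-study visit after 13 weeks, allows for determining the duration of intervention needed for microbiota and metabolite shifts"; and, for cognition, "mid-study effects on cognition by NTB will allow for insights into timing of onsets of potential protective cognitive effects". Nothing in section 2.9.1 uses week 13.

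**The concern.** Three features of one paragraph need attention.

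- **Baseline.** Under randomisation the arms share a baseline mean in expectation, and section 2.6 places all baseline measurements before the first supplement. A model with a separate baseline mean per arm does not use that fact. The primary analysis in the same section does use the baseline.
- **Week 13.** The article itself fixes the timepoints, and they exclude a wave that it presents as a design strength. An analysis that follows section 2.9.1 literally yields no week-13 contrast, and one added after the results are known would be post hoc.
- **Testing order.** The paragraph compares each fibre individually with placebo, then appears to make fibre-specific tests depend on a significant interaction. If the first phrase means separate two-arm models, the post-hoc step is redundant. If it means one four-arm model, the fibre tests are gated.

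At stake are some power on every outcome analysed this way, and a prespecified answer on timing. Precision matters a little more because 151 were randomised (section 3) against a planned 164 (section 2.5).

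**Working it through.** **Inputs.** Model terms and timepoints: section 2.9.1. Dropout of 15%: section 2.5. Randomised: 151, or 37.75 per arm on average (section 3). Week-13 subset: 80, about 20 per arm if evenly spread (assumed). The correlation rho between baseline and week 26 is not given, so a range is assumed. The article states no precision or power for this model, so there is no figure to reproduce; the sample size in section 2.5 is for a different analysis and is not used.

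**Step 1: what the interaction estimates.** With two complete waves, a random intercept and group, time and group x time, the interaction equals the difference in mean change. Fitted to simulated data, the two agreed to about 1e-15.

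**Step 2: variance with complete data.** With unit SD at both waves, the variance is proportional to 2(1 - rho) for the change score and to 1 - rho² for baseline adjustment. The ratio is 2/(1 + rho). Simulation with 38 per arm gave 1.36, 1.21 and 1.06 at rho 0.5, 0.7 and 0.9, against 1.33, 1.18 and 1.05 by formula.

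**Step 3: variance with dropout.** Let n per arm have a baseline and m per arm a week-26 value, under compound symmetry and ignorable dropout. Per arm, the free-baseline model has variance (1 - rho²)/m + (1 - rho)²/n and the common-baseline model (1 - rho²)/m. The ratio is 1 + (m/n)(1 - rho)/(1 + rho), here with m/n = 0.85. At rho 0.5: 1 + 0.85 × 0.333 = 1.28.

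| Assumed rho | Excess variance, complete data | Excess variance, 15% dropout |
|---|---|---|
| 0.5 | 33% | 28% |
| 0.6 | 25% | 21% |
| 0.7 | 18% | 15% |
| 0.8 | 11% | 9% |
| 0.9 | 5% | 4% |

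**Step 4: what this means for power.** For an assumed 0.5 SD difference, 37.75 per arm, complete data and unadjusted two-sided 0.05, power is 58% against 71% at rho 0.5, 80% against 86% at 0.7, and 93% against 95% at 0.8 (stated model first, baseline-adjusted second). Example at rho 0.5: the standard errors are √(2 × 1.00/37.75) = 0.230 and √(2 × 0.75/37.75) = 0.199.

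**Step 5: what week 13 adds.** Including it leaves the week-26 contrast unchanged with complete data and improves its precision by about 1-2% with 15% dropout. Its value is the week-13 contrast itself. With 20 per arm at week 13, 37 per arm otherwise and a common baseline, the variance is 0.071 SD² at rho 0.5 and 0.047 at 0.7. The 95% half-widths are 1.96 × √0.071 = 0.52 SD and 1.96 × √0.047 = 0.42 SD.

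**Step 6: the gate.** Taking 151 × 0.85/4 ≈ 32 per arm, an assumed standardised difference of 0.60 and Benjamini-Hochberg over three contrasts, simulated power per active contrast was 0.489 ungated and 0.470 gated with one active fibre, and 0.595 and 0.551 with all three active. The cost is about 2-4 percentage points.

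**Step 7: what is measured at week 13.** Table 3 marks BDNF and blood tryptophan metabolites at baseline, week 13 and week 26. Section 2.8.1.3 gives only baseline and week 26 for both. The two places disagree.

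**The case against.** The strongest defence is that the model fits the stated objectives. Every objective in section 2.1 and Table 1 concerns 26 weeks. Many secondary outcomes (cortisol, the amyloid ratio, NfL, GFAP, structural MRI, cytokines, lipids, barrier and intestinal inflammation markers) have no week-13 measurement, so two waves is the only structure common to all. A group x time mixed model is standard and unbiased, and the analysis of a subset can be left to an analysis plan. The loss is also small where outcomes are stable over time.

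Most of this stands and limits the point. It does not remove it: the article chose the timepoints explicitly and elsewhere promises findings from the wave it left out, and using the baseline already collected costs nothing.

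Three stronger readings are tempting but unsupported.

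- A reader might infer that the trial fails a formal week-13 objective. There is none; the expectation appears in the Discussion.
- A reader might infer that a fibre that works alone may never be tested. In the one-active-fibre simulation the overall test passed about 68% of the time, and the gate cost only about 2 points of power.
- A reader might infer that the subset's extra exposure to the cognitive tests biases week 26. It would do so only if subset membership differed by arm or practice interacted with arm. The article indicates neither.

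**Conclusion.** The point holds as a moderate, easily corrected weakness. The stated model is valid but gives away precision: 5 to 33% excess variance with complete data, or 4 to 28% with 15% dropout, over correlations from 0.9 down to 0.5. Which end applies will vary by outcome and cannot be told from the article. The 15% allowance includes fMRI quality losses, so dropout for other outcomes may be smaller. The figures assume equal variances at both waves and ignorable dropout. That baseline means are free is inferred from group being a fixed factor beside time, which is the ordinary reading.

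The week-13 conflict is real but confined to a supplementary aim. It does not weaken the 26-week results, and any week-13 estimate will be imprecise. On the gate, the unclear wording matters more than the power cost.

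**What to change.** For secondary and tertiary outcomes suited to a linear model:

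1. Fit one four-arm model with a common baseline mean across arms, or with baseline as a covariate. Report the three fibre-minus-placebo contrasts at week 26 with the Benjamini-Hochberg adjustment already planned.
2. Where week 13 was measured, enter time as categorical with three levels. Report the week-13 contrasts as a supplementary analysis of onset, stating the number per arm and the expected imprecision.
3. State whether fibre-specific contrasts are tested directly or only after a significant overall interaction. Direct testing is preferable, since multiplicity is already handled.
4. Reconcile Table 3 with section 2.8.1.3 on whether BDNF and tryptophan metabolites are measured at week 13.

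The cost is analysis-plan wording and slightly more modelling, with no new data. It should be settled before unblinding.

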#### Data management and confidentiality

2.9.2

Data from study visits, measurements and questionnaires will be captured online in CASTOR EDC (127) and verified by two researchers where possible. Participants will receive a unique identification number, used to label all collected data and biological samples. Published data will not be traceable to the identification number. Personal details will be stored separately in secure digital file. Signed informed consent forms and printed questionnaires will be stored in a secure locker. Personal data and biological material, will be retained for 15 years following study completion, after which it will be destroyed. The handling of personal data will comply with the EU GDPR and the Dutch Act on Implementation of the GDPR.

#### Dissemination

2.9.3

Finding from this trial will be published in accordance with the CCMO’s publication statement. All parties within the study consortium have agreed upon the CCMO directive. Findings from this trial will be disseminated through peer-reviewed, open access publications, conference presentations, and submission to relevant trial registries and databases. Results will be shared with participating institutions and funding partners. Neither the subsidising parties, nor the principal investigator has a right of veto regarding the way of publishing the results. Partners have the right to take cognizance of the results in order to patent some of the outcomes if applicable

## Initial results

3

By July 2025, baseline measurements were successfully completed. In total, 151 volunteers were randomized into one of four arms and started the intervention. The mean age of our population was 69.4 years (SD = 4.8) and the population consisted of 47.7% females (*n* = 72). The average number of modifiable risk factors was 3.05 (SD = 0.93) and the mean BMI in the population was 27.91 kg/m^2^ (SD = 3.87). Most of the participants (55.6%, *n* = 84) were highly educated, as defined by having at least a 2-year associate degree at a University of Applied Sciences [in Dutch: Hoger Beroeps Onderwijs (HBO)]. Of all subjects, 37.7% carried one or more APOE ε4 allele. The mean MoCA score was 26.09 out of 30 (SD = 2.30) and the average habitual dietary fibre intake was estimated to be 23.68 grams per day (SD = 8.22). Baseline characteristics per intervention arm are presented in Table 6.

**Table 6 tab6:** Baseline characteristics.

		Total	Intervention group			
			A	B	C	D
		*n* = 151	*n* = 37	*n* = 38	*n* = 38	*n* = 38
Sex	% female	47.7	45.9	47.4	50.0	47.4
Education level	% 2-year HBO associate degree or higher	55.6	59.5	44.7	47.4	71.1
APOE genotype	% ε4 carrier	37.7	45.9	39.5	39.5	26.3
Age	mean (sd)	69.4 (4.8)	69.9 (4.7)	69.1 (4.6)	68.5 (4.4)	69.9 (5.6)
Number of risk factors	mean (sd)	3.05 (0.93)	3.03 (0.83)	3.03 (0.85)	3.11 (0.98)	3.03 (1.08)
BMI (kg/m^2^)	mean (sd)	27.91 (3.87)	28.0 (3.88)	28.0 (4.78)	28.2 (3.47)	27.5 (3.30)
Habitual fibre intake (g/day)	mean (sd)	23.68 (8.22)	22.76 (9.29)	23.08 (7.92)	23.91 (6.61)	24.99 (8.94)
MoCA score (max 30)	mean (sd)	26.09 (2.30)	26.16 (2.36)	25.55 (2.81)	26.45 (1.93)	26.18 (2.00)

APOE, Apolipoprotein E; SD, standard deviation; BMI, body mass index; MoCA, Montreal Cognitive Assessment.

## Discussion

4

The PRECODE study will provide an in-depth evaluation of the microbiota-gut-brain axis in older adults, at risk of cognitive decline. Through targeting modulation of the gut microbiota and metabolites by dietary fibres, this study aims to evaluate potential protective effects in SCD+. Repeated failures of disease-modifying treatments in age-related neurodegenerative conditions have highlighted the urgent need to prioritise prevention over late-stage intervention. The study hereby addresses knowledge gaps needed for advancement of preventative strategies.

The study population of individuals with SCD + and additional life-style (LIBRA-score) risk factors, is ideally suited as a target cohort to evaluate potential protective roles on cognition, as individuals are by definition clinically unimpaired. SCD is considered a compensatory phase in preclinical AD, where neural compensation mechanisms may mask functional deficits, and subtly worse performance in neuropsychological tests are seen compared to healthy controls (112–114, 117). The study design allows for the assessment of these subtle cognitive deficits, as both the primary outcome measure, 2-back task during fMRI scanning, and secondary outcome NTB subscales, are sensitive to detect these early cognitive changes (112, 117). Additionally, the 26-week duration of the intervention aligns with previous studies demonstrating significant effects on memory in SCD (241).

The investigation of this cohort is further strengthened by the measurement of AD-related markers, such as ApoE4 ε4 genotype and plasma Aß 41/42 ratios, which indicate a further increased risk of progression to AD (113, 114). Additionally, GFAP and NfL measurements, indicative of neuroglial reactivity and neuraxial injury, respectively (200, 202), will offer insights into potential neuroprotective mechanisms of fibre supplementation, and may provide novel understandings of the role of these emerging biomarkers along the MGBA. Baseline characterisation will allow for subgroup analyses in ApoE ε4 -carriers vs. non-carriers. Recent cross-sectional studies suggest differing cognitive protective effects of dietary fibre based on ApoE-genotype (242). Our study may further elucidate genotype-specific dietary fibre effects along the MGBA, that may pave the way for personalised nutrition approaches in high-risk individuals.

A further major strength of the PRECODE study design lies in the multidomain, mechanistic nature. In-depth exploration of multiple outcomes integrating neuroimaging, microbial, metabolic, and cognitive endpoints, allows for a more complete characterisation of MGBA pathways. Notably, this provides a unique opportunity to investigate associations between gut-derived changes and both functional and structural brain effects, as neuroimaging-omics approaches are lacking in human preclinical AD research (243, 244). PRECODE enables correlation analyses between gut microbial composition, microbial metabolites (SCFAs, indoles), and brain outcomes such as functional connectivity, vascular response, and regional brain volume, within the context of working memory performance. Biomarkers such as BDNF, cortisol, and inflammatory cytokines will support investigation into systemic mechanisms linking the gut and brain. Furthermore, measurements of glycaemic control and insulin resistance, which predict cognitive decline, will allow examination of metabolic pathways contributing to neuroprotection (158, 245).

Targeted metabolite analysis of SCFAs and tryptophan-derived indoles, further strengthens mechanistic insights into how microbiota-derived compounds may modulate brain health. The use of multiple biomatrices, such as SCFA measurement in both blood and faeces, will allow for quantification of systemic absorption and may provide more precise associations with cognitive outcomes. Favourable indoles, such as IPA and indole lactic acid, display potent antioxidant and anti-inflammatory properties and may inhibit Aβ aggregation (82, 211, 246). These effects are partly mediated through activation of the immunomodulatory aryl hydrocarbon receptor (AhR) receptor, a regulator of neuroinflammation (247–249). Preclinical studies suggest that AhR activation by indoles promotes youthful gene expression profiles, and extends healthy lifespan (250). PRECODE may thus provide novel insights into the potential protective roles of these metabolites in early cognitive ageing and healthspan promotion, supporting their investigation as candidate biomarkers. In addition, distinct microbial and metabolite signatures may be identified, that can inform on mechanistic pathways as well as cohort classification in preclinical AD.

The inclusion of a mid-study visit after 13 weeks, allows for determining the duration of intervention needed for microbiota and metabolite shifts. Furthermore, mid-study effects on cognition by NTB will allow for insights into timing of onsets of potential protective cognitive effects. Moreover, sex, ApoE genotype and age, influence AD disease stage progression (251). Here, further valuable information on whether these factors may influence the trajectory of potential interventions may be highlighted. Moreover, should there be any significant association evidenced between microbial compositional change and cognitive performance, it might be worthwhile to conduct a follow-up investigation, in which we research if and how long potential microbiota changes last after the trial has been finished, and to compare E4 vs. non-E4 carriers and relatedness of the number of LIBRA risk factors.

Despite its strengths, the study has potential limitations. The self-reported and progressive nature of SCD + may introduce heterogeneity, such as the potential inclusion of individuals with undiagnosed depression and anxiety that may mimic cognitive decline (114, 252). Clinical depression and anxiety are excluded at screening, and will be further assessed by GDS-15 and GAD-7 scores at baseline. Furthermore, some individuals may potentially convert to amnestic MCI over the course of the intervention, which will be evaluated by end-NTB results. Inclusion criteria, such as requirements for general and technological literacy, may additionally introduce bias towards individuals with higher education or better cognitive function. In addition, the inclusion criterion of at least 2 LIBRA risk factors next to presence of SCD may overall limit the generalizability of our findings to SCD individuals with fewer or different combinations of lifestyle risk factors, and should not be generalized to the entire preclinical AD spectrum. Next, long-term fibre supplementation in older adults with increased gastrointestinal sensitivity, may lead to study withdrawal, for which a 15% drop-out rate has been included. Strategies such as dose tapering, morning and evening dosing, and telephone check-ins are used to promote adherence. Furthermore, due to the scope of inclusion and exclusion criteria, including MRI compatibility, extensive recruitment efforts might be needed.

To our knowledge, PRECODE is the first human study to investigate the combined cognitive and microbial effects of three distinct dietary fibres- chicory inulin, resistant dextrin and seaweed polysaccharide, in SCD+. The extensive mechanistic and functional outcomes will provide valuable insights into the role of the MGBA in preclinical cognitive decline, advancing the field of nutrition-based prevention in cognitive ageing and contributing toward the development of personalised strategies in preclinical AD.

